#### Economic evaluation

To examine the cost-effectiveness of the SOLAR intervention, an economic evaluation including both cost-effectiveness and cost-utility analysis will be completed. The evaluation will be conducted in a manner consistent with the guidelines published by the Health and Information Quality Authority in Ireland [15]. The objectives of the evaluation will be to identify, quantify and compare the costs and outcomes of the SOLAR intervention relative to usual care. The costs will reflect those falling on the health and social care system such as return ED visits, inpatient stays, GP visits, medications prescribed and public health nurse visits. The primary and secondary outcomes outlined in the trial will be utilised with regard to intervention effectiveness. The marginal costs and effects of the programme relative to standard care will be calculated through incremental analysis and used to estimate relevant incremental cost-effectiveness ratios. Furthermore, the cost-utility analysis will use patient responses to the EuroQol EQ-5D measurement tool to estimate effectiveness in terms of Quality Adjusted Life Years (QALYs). Budget-impact analyses for the alternative ED patient care approaches will be undertaken. Uncertainty in the estimates will be examined using multivariate sensitivity analyses while cost-effectiveness acceptability curves will also be presented.

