**Methods:**

This will be a parallel 1:1 allocation randomised control trial. All patients who are ≥ 75 years will be screened for frailty using the Identification of Seniors At Risk (ISAR) tool. Those with a score of ≥ 2 on the ISAR will be randomised. The treatment arm will undergo geriatric medicine team-led CGA in the ED or Acute Medical Assessment Unit whereas the non-treatment arm will undergo usual patient care. A dedicated multidisciplinary team of a specialist geriatric medicine doctor, senior physiotherapist, specialist nurse, pharmacist, senior occupational therapist and senior medical social worker will carry out the assessment, as well as interventions that arise from that assessment. Primary outcomes will be the length of stay in the ED or Acute Medical Assessment Unit. Secondary outcomes will include ED re-attendance, re-hospitalisation, functional decline, quality of life and mortality at 30 days and 180 days. These will be determined by telephone consultation and electronic records by a research nurse blinded to group allocation.

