### Outcomes{12}

The primary outcome of the study is patient ED length of stay or Patient Experience Time (PET) time, which is recorded as time of arrival at the ED until discharge from ED to home or admission to a ward. For participants in the AMAU, this is defined as the time from arrival at the hospital to discharge from AMAU or admission to a medical ward.

Secondary outcomes include mortality, ED revisit, unplanned hospital visit(s) or nursing home admission within 30 days and 6 months of initial index visit. Healthcare utilisation will also be captured at 30 days (GP visit, Public Health Nurse visit, Allied Health Services) by telephone contact. Follow-up at 30 days and 6 months will be captured by telephone contact by a research nurse who is blinded to group allocation. Patient reported outcomes at 30 days include a global measure of function (Barthel Index) and quality of life survey (EuroQoL-5D EQ-5D) [13, 14]. In addition, patient satisfaction with their index visit will be explored using a patient satisfaction questionnaire. A detailed process evaluation will be completed using a mixed methods approach. The process evaluation will explore stakeholders’ experience of implementing the intervention as well as examining factors that enabled or hindered the delivery of same.

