## Statistical methods

### Statistical methods for primary and secondary outcomes {20a}

Appropriate descriptive statistics will be used to describe the baseline characteristics of study participants. These will include proportions, percentages, ranges, means and standard deviations and medians and interquartile ranges (where data are not normally distributed). We will analyse differences across the two groups for all continuous outcomes (ED length of stay, etc.) by using independent samples *t* tests with 95% confidence intervals. The non-parametric equivalent, the Mann-Whitney test, will be used for skewed data.

Incidence of ED return, unplanned hospital admission, nursing home admission and healthcare utilisation will be explored using crude and adjusted risk ratios with associated 95% confidence intervals using logistic regression. Unit costs will also be applied to resource use data. The total costs of health and social care input will be compared between groups with complete resource utilisation data, using non-parametric bootstrapping (it is anticipated that the data will be highly skewed in terms of distribution). A 5% level of statistical significance will be used throughout the analyses.

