### Methods in analysis to handle protocol non-adherence and any statistical methods to handle missing data {20c}

An intention to treat analysis using linear mixed models will be used to compare outcomes between the intervention and control arm and account for the correlation within-subject over time, while adjusting for differences in participant characteristics at baseline where appropriate. A sensitivity analysis, via multiple imputation, will be used to explore whether adherence to the intervention influences the effect of the intervention on the primary outcome.

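### The complete-case rule for costs is liable to drop participants who die before the 30-day call, and no rule says how a death enters the QALYs, so the economic comparison may not be one of the randomised groups

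*Protocol article*

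**What the plan says.** All references are to the protocol article.

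- **Costs.** Section {20a} states: "The total costs of health and social care input will be compared between groups with complete resource utilisation data". Bootstrapping is planned because costs are expected to be skewed.
- **Where resource use comes from.** Outcomes {12} collects GP, public health nurse and allied health contacts by telephone at 30 days. The Economic evaluation section counts GP and public health nurse visits among the costs, with return ED visits, inpatient stays and medications.
- **QALYs.** The Economic evaluation section says "the cost-utility analysis will use patient responses to the EuroQol EQ-5D measurement tool to estimate effectiveness in terms of Quality Adjusted Life Years".
- **Function and quality of life.** Outcomes {12}: "Patient reported outcomes at 30 days include a global measure of function (Barthel Index) and quality of life survey" (the EQ-5D). The abstract lists these outcomes at 30 and 180 days.
- **Mortality.** Outcomes {12}: "Secondary outcomes include mortality, ED revisit, unplanned hospital visit(s) or nursing home admission within 30 days and 6 months of initial index visit".
- **Non-responders.** Section {11b} continues to collect data that need no contact with the participant, such as hospital database records.
- **Analysis principle.** Section {20c}: "An intention to treat analysis using linear mixed models will be used to compare outcomes between the intervention and control arm".

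No section says how a death enters the cost, QALY, EQ-5D or Barthel comparison.

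**The concern.** Participants are aged 75 or over and screened as at risk, and mortality is a planned outcome, so some deaths before the 30-day call are to be expected. Such a participant cannot report community contacts. Under a complete-case rule their costs are then liable to leave the comparison altogether, including the ED and inpatient costs that the hospital holds.

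Those who remain were selected after randomisation. If survival differs between arms, or if CGA changes the costs of people who die, the difference among the remainder is not the effect in the groups as randomised. The same applies to QALYs if utilities are taken only from respondents, although death has a known utility of 0 and generates no later costs. Cost-effectiveness is part of the trial's overall aim. Ratios and acceptability curves depend on point estimates and their joint distribution, so a modest shift can matter there even when no significance test changes.

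**Working it through.** **1. The sections side by side.** {20a} requires complete resource-use data. {12} obtains part of it from the 30-day call. A death before the call leaves that part unreported unless a proxy supplies it. {11b} keeps the hospital part, but {20a} then has no use for it. {20c} promises intention to treat. The cost rule is written down, so an analysis plan would have to reverse it; it could not merely add detail.

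**2. How many are affected.** The documents give no death rate, so 5%, 10% and 20% are assumed. With 118 per arm (section {14}), 5.9, 11.8 or 23.6 control participants would be liable to exclusion if all died before the call. Deaths after the call do not lose the 30-day report.

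**3. Costs, in symbols.** Let mc and mt be the death rates under control and CGA, and δ = mc − mt. Let Cs, Ce and Cd be the mean costs of those who survive in either arm, of the extra CGA survivors, and of those who die. Assume no other effect of CGA on costs.

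- Complete cases: δ(Ce − Cs)/(1 − mt)
- All randomised: δ(Ce − Cd)

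If Ce = Cs, the first is 0 and the second is δ(Cs − Cd). The documents give no unit costs and do not say whether people who die cost more or less than survivors, so the sign of the bias is open. At mc = 10% and a risk ratio of 0.92, mt = 9.2% and δ = 0.8%. The omitted term is then 0.8% of the cost gap between survivors and those who die.

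**4. Function and utility.** Assumptions: control deaths 10%; Barthel on a 0–100 scale, mean 75 and SD 20 in those who survive in either arm, 45 in the extra survivors; utility 0.60 and 0.35 respectively; no other effect of CGA. The risk ratios are the estimate and 95% limits (0.55 to 1.52) that the Background quotes from its systematic review of CGA in the ED.

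- Survivors only: δ(b − B)/(survivor share of the arm with fewer deaths)
- Death scored 0: δ × b

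Here B is the mean in those who survive in either arm and b the mean in the extra survivors. For a risk ratio above 1 the extra survivors are in the control arm and δ is negative.

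| Risk ratio | CGA deaths | δ | Barthel, survivors | Barthel, death = 0 | Utility, survivors | Utility, death = 0 |
|---|---|---|---|---|---|---|
| 0.55 | 5.5% | 4.5% | −30×0.045/0.945 = −1.43 | +2.03 | −0.012 | +0.016 |
| 0.92 | 9.2% | 0.8% | −30×0.008/0.908 = −0.26 | +0.36 | −0.002 | +0.003 |
| 1.52 | 15.2% | −5.2% | −30×(−0.052)/0.900 = +1.73 | −2.34 | +0.014 | −0.018 |

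The standard error of the survivor Barthel difference at 0.92 is about 20 × √(1/106.2 + 1/107.1) = 2.7, so −0.26 is about 0.1 of it.

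Varying control deaths at a risk ratio of 0.92:

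- 5%: −30×0.004/0.954 = −0.13 points
- 20%: −30×0.016/0.816 = −0.59 points

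If the extra survivors are as well as everyone else (b = B), the survivor contrast is exactly 0 in every row.

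**5. QALYs over 180 days** (T = 180/365.25 = 0.493 years), 10% v 9.2% deaths. Utility starts at 0.60 and falls linearly to 0.35 in extra survivors (average 0.475) and to 0 in those who die (average 0.30).

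- Survivors only: (0.475 − 0.60) × 0.493 × 0.008/0.908 = −0.0005
- All randomised: 0.008 × (0.475 − 0.30) × 0.493 = +0.0007

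**The case against.** The best reply is that most of this is silence, and how deaths enter QALYs and function is commonly left to an analysis plan or health-economic plan, neither of which is shown. That stands for QALYs and Barthel. Taking utilities from patient responses does not bar a value of 0 from a recorded date of death, and the evaluation is to follow a national guideline whose content is not shown. It does not stand for costs, where a complete-case rule is stated.

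Second, resource use does not rest on the telephone alone. The abstract adds electronic records, section {18b} allows next of kin to help with calls, and ED and inpatient use is in hospital systems. This narrows the loss to community contacts. But if completeness is required of the whole record, a missing community part still removes the hospital part. A participant whose use is known up to death might be read as complete; the text does not say so.

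A reader might infer that a survival benefit would be hidden. The documents do not support that: mortality is reported separately, and the Economic evaluation section uses the primary and secondary outcomes as effectiveness measures. A reader might also fear that multiple imputation would fill in Barthel or EQ-5D after death, but {20c} plans it only for adherence and the primary outcome. The mixed model in {20c} keeps a dead participant's baseline score, but treats the later score as ordinarily missing, so it does not resolve the point.

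**Conclusion.** The point holds for the cost comparison as written, and conditionally for QALYs: if they are built only from EQ-5D respondents, they share the defect. In either case the comparison is not one of the randomised groups and could be biased if survival differs.

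Size and sign cannot be derived from the documents. At the quoted risk ratio of 0.92 the illustrated shifts are small: −0.13 to −0.59 Barthel points for control deaths of 5% to 20%, and less than 0.001 QALY either way at 10%. Across the quoted confidence interval the sign itself changes.

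It is tempting to say that a survival benefit would show as worse function, or that the cost-effectiveness result would take the wrong sign. The documents support neither. The first needs both a survival difference and frailer extra survivors. For the second, no cost, utility or death rate is given from which a ratio could be computed.

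**What to change.** - **Section {20a}.** Replace the complete-case rule with a comparison of all randomised participants. Costs accrue to the date of death from hospital records and available reports, with none afterwards. Show the complete-case result as a sensitivity analysis.
- **Economic evaluation.** State that utility is 0 from the date of death.
- **Function.** State that a Barthel comparison among survivors is not a randomised comparison, and present it beside mortality. A composite with death is optional: scoring death at the lowest Barthel value is one defensible estimand among several, and it mixes in an outcome already reported separately.

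The change is a few sentences, and vital status is already collected. The cost is that some community resource use before death must be imputed or obtained from proxies, which brings its own assumptions.

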### Concealment mechanism {16b}

Allocation will be concealed from participants and researchers until both consent has been obtained and baseline evaluations has been performed. After allocation is revealed, the intervention will be organised by the team.

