## Data collection and management

### Plans for assessment and collection of outcomes {18a}

All participants will undergo a baseline assessment by the research nurse to include a global measure of function (Barthel Index) and quality of life (EuroQoL-5D [EQ-5D]).

Participants who are allocated to the SOLAR team CGA assessment and intervention will additionally be assessed by one or more members of the interdisciplinary SOLAR team who will complete a detailed clinical assessment including but not limited to managing medical issues and medication review, assessment of mobility and stairs, transfer, personal care, activities of daily living (ADLs), social supports, and cognition. Clinicians will be guided by their clinical expertise and codes of professional practice when completing the assessment.

Similarly, interventions prescribed by the SOLAR team will be based on subjective and objective assessment of patients and will include onward referral as appropriate. All assessments and interventions by the SOLAR team will be included in the medical chart, as is routine clinical practice to inform their medical care. Details of SOLAR assessment and intervention will be collected for the purposes of this study.

Data collection forms will be stored in a data repository and are provided as an appendix to this protocol. Hard copies of the consent form and completed questionnaires will be securely stored in a locked cabinet in a building requiring swipe card access.

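### No stated rule secures adjustment of the incremental QALY for pre-randomisation EQ-5D, although the score is already collected and adjusting for it would sharpen the estimate at no cost

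*Protocol article*

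**What the plan says.** All statements are in the protocol article.

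- **Source of the QALY** (Outcomes {12}, Economic evaluation): "the cost-utility analysis will use patient responses to the EuroQol EQ-5D measurement tool to estimate effectiveness in terms of Quality Adjusted Life Years". Marginal costs and effects come from an incremental analysis that feeds ICERs and acceptability curves. On method the section defers to a national guideline: "The evaluation will be conducted in a manner consistent with the guidelines published by the Health and Information Quality Authority in Ireland". It gives no area rule, time horizon or covariate.
- **Baseline EQ-5D** (section {18a}): "All participants will undergo a baseline assessment by the research nurse to include a global measure of function (Barthel Index) and quality of life", the latter by EQ-5D. This precedes allocation (section {16b}): "Allocation will be concealed from participants and researchers until both consent has been obtained and baseline evaluations has been performed".
- **Follow-up EQ-5D**: Outcomes {12} says "Patient reported outcomes at 30 days include a global measure of function (Barthel Index) and quality of life survey", again EQ-5D. The Abstract, under Methods, lists among the secondary outcomes "functional decline, quality of life and mortality at 30 days and 180 days".
- **Comparison rule** (section {20a}): "We will analyse differences across the two groups for all continuous outcomes (ED length of stay, etc.) by using independent samples" t tests, with Mann-Whitney for skewed data.
- **Costs** (section {20a}): "The total costs of health and social care input will be compared between groups with complete resource utilisation data, using non-parametric bootstrapping".
- **Baseline adjustment** (section {20c}): an intention-to-treat linear mixed model for outcomes over time, adjusted for baseline differences only where judged appropriate.

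**The concern.** For a 30-day EQ-5D score, ignoring baseline costs precision and no more. A QALY built as an area under the utility curve is different, because the pre-randomisation score is then part of the outcome. Any chance difference between arms at enrolment, which the intervention cannot have caused, enters the effect estimate directly. It also enters indirectly, through its correlation with the follow-up score.

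Over many randomisations the unadjusted difference is still unbiased. What is at stake is precision, and how far the estimate in this one trial is displaced by the imbalance that happens to occur. The QALY difference is the denominator of the cost-utility ratio. Over a 30-day horizon any real gain is a few thousandths of a QALY, so a chance term of similar size can change the ratio greatly or reverse its sign.

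**Working it through.** **Inputs from the article.** 118 per arm and 20% attrition (Sample size {14}). The 118 reproduces: a two-sample t test with difference 9.31 h, SD 19.91 h, 90% power and two-sided 0.05 needs 98 per arm, and 98 × 1.2 = 117.6, or 118. Patients with follow-up: 118 × 0.8 = 94.4, so 94 per arm. The article gives no figure for EQ-5D or QALYs.

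**Assumptions.** Utility SD *s* from 0.20 to 0.35, equal at all visits; correlation *r* between visits from 0.3 to 0.7; straight-line area between visits.

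**1. Weight of baseline, visits at 0 and 30 days (Outcomes {12}).** QALY = T(U0 + U1)/2 with T = 30/365.25 = 0.0821 years. Baseline carries exactly one half.

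**2. Size of chance imbalance.** SE of the baseline difference = *s*√(2/n). Its direct contribution to the QALY difference is T/2 = 0.0411 times the imbalance.

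| s | n per arm | SE of imbalance | 95% range, utility | 95% range, QALY |
|---|---|---|---|---|
| 0.20 | 118 | 0.0260 | ±0.051 | ±0.0021 |
| 0.20 | 94 | 0.0292 | ±0.057 | ±0.0024 |
| 0.30 | 94 | 0.0438 | ±0.086 | ±0.0035 |
| 0.35 | 118 | 0.0456 | ±0.089 | ±0.0037 |
| 0.35 | 94 | 0.0511 | ±0.100 | ±0.0041 |

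**3. Comparison with a true gain at 30 days.** The gain in QALY is 0.0411 × the utility gain. The last column is the probability that the absolute imbalance exceeds the gain, over the whole range of *s* and n.

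| Utility gain | QALY gain | Probability |
|---|---|---|
| 0.03 | 0.0012 | 25 to 56% |
| 0.05 | 0.0021 | 5 to 33% |
| 0.07 | 0.0029 | 1 to 17% |
| 0.10 | 0.0041 | 0 to 5% |

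**4. What adjustment gains, visits at 0 and 30 days.** Per-person variance of the QALY, unadjusted: T²s²(1 + r)/2. Given U0: T²s²(1 − r²)/4. The ratio is (1 − r)/2. With s = 0.30 and 94 per arm:

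| r | SE unadjusted | SE adjusted | Variance ratio |
|---|---|---|---|
| 0.3 | 0.0029 | 0.0017 | 0.35 |
| 0.5 | 0.0031 | 0.0016 | 0.25 |
| 0.7 | 0.0033 | 0.0013 | 0.15 |

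The SE is 1.7 to 2.6 times smaller with adjustment.

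**5. Visits at 0, 30 and 180 days (Abstract).** The trapezoid weights are 15/180 = 1/12, 90/180 = 1/2 and 75/180 = 5/12, so baseline carries 8.3%. The sum of squared weights is 62/144 = 0.4306. In units of *s*² over the 180 days, with common *r*:

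- variance of the QALY = 0.4306 + 0.5694r
- covariance with baseline = 1/12 + (11/12)r
- variance ratio = 1 − covariance²/variance

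At r = 0.5 this is 1 − 0.5417²/0.7153 = 0.59. At r = 0.3 it is 0.79, and at r = 0.7 it is 0.37. The direct chance term stays at ±0.0035 QALY for s = 0.30 and 94 per arm, but a 0.05 gain reached at 30 days and sustained is now worth 0.05 × 165/365.25 = 0.0226 QALY.

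**The case against.** The strongest objection is that an article commonly leaves QALY construction, utility covariates and resampling to an analysis plan or health-economic plan, and that the cited guideline may settle them. This stands so far as it goes: the missing area rule and horizon are no error. But the article does state a rule for all continuous outcomes, and it is unadjusted. It states a second rule in {20c}, and that one is conditional. Neither secures adjustment for baseline utility.

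It can also be said that the mixed model in {20c} could deliver a QALY difference as a weighted sum of visit estimates, with baseline adjustment. It could. But adjustment that depends on judging whether the arms differ is not fixed in advance.

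Four stronger readings are tempting, and the article does not support them:

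- **That the plan specifies an unadjusted QALY difference.** Economic evaluation is silent. The unadjusted rule in {20a} reaches QALYs only by extension.
- **That imbalance can swamp any plausible gain.** For a 0.10 utility gain it does so at most about 5% of the time. On the 180-day schedule, a sustained 0.05 gain is about six times the 95% chance term (0.0226 against 0.0035).
- **That the QALY ratio is the main economic result.** Nothing ranks it above ratios based on the trial's primary and secondary outcomes.
- **That ICERs will rest on a bootstrap of costs alone.** The sentence in {20a} describes the between-group comparison of total costs. It does not exclude paired resampling for the ICER.

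**Conclusion.** The point holds as a free improvement to the analysis. The plan as written does not guarantee that the incremental QALY is adjusted for a score that every participant gives before allocation.

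If the {20a} rule is applied to a straight-line QALY over baseline and 30 days, chance imbalance adds up to about ±0.002 to ±0.004 QALY. That is comparable to a small true gain (0.0012 to 0.0021 QALY for 0.03 to 0.05 in utility). Adjustment would reduce the variance to 0.35, 0.25 or 0.15 of its unadjusted value at r = 0.3, 0.5 or 0.7.

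If quality of life is also measured at 180 days, imbalance matters much less, but the ratios of 0.79, 0.59 and 0.37 still favour adjustment. The recommendation therefore does not depend on which schedule is right, although its size does.

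The utility SD, the correlation, the true gain and the area rule are all assumed, since the article gives none of them. The Abstract and Outcomes {12} disagree on whether quality of life is measured at 180 days. The legend of Fig. 1 mentions 180-day outcomes without naming them, and the figure itself was not in the text reviewed.

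**What to change.** 1. In Economic evaluation and section {20a}, state that the incremental QALY is the arm coefficient from a regression of QALY on arm and baseline EQ-5D utility, in all cases and regardless of observed imbalance.
2. State that this regression is run within the bootstrap used for the ICER and the acceptability curve, with each participant's cost and QALY resampled together.
3. Reconcile the Abstract with Outcomes {12} on whether quality of life is measured at 180 days, and state the QALY horizon that follows.

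Items 1 and 2 cost a sentence or two of analysis text and a few lines of code. Baseline EQ-5D is already planned for everyone, so they need no extra patients, visits or staff. Item 3 is a correction of wording once the investigators confirm which schedule applies.
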